#### Secondary outcomes

Loss to follow-up has been very low so far, i.e., < 5% at 24 months and a 7-year cohort study conducted in the same region had a follow-up rate of 92% [30]. Assuming missing data (i.e., no lost outcome data due to reasons such as loss-to-follow-up or no blood sample) reaches 18% in the control arm and 22% in the intervention arm, 415 and 390 participants in the control and intervention arm, respectively are predicted to provide data at 9-years of follow-up. With the sample sizes of 415 and 390 participants in the control and intervention arms respectively, we shall be able to detect an effect size (i.e., the absolute difference in means divided by standard deviation) in other continuous outcomes (e.g., anthropometric, BP, microvascular and cholesterol measurements) of 0.23 with 80% power at the two-sided 5% significance level, when accounting for an intra-cluster correlation of 0.02. Power was derived using power *twoprop* and *clustersampsi* in Stata software (version 17 StataCorp LP, College Station, TX, USA).

### Intervention

Detailed description of the cultural adaptation and development of the K-DPP intervention has been published previously [6, 31]. Briefly, K-DPP involved a 12-month peer-support program that consisted of 15 group sessions: an introductory session delivered by the K-DPP team; two education sessions conducted by local experts; and 12 sessions delivered by trained lay peer leaders. Group sessions were held in the local community in a convenient neighbourhood facility and at convenient time during weekends. The peer group sessions aimed to increase physical activity, promote healthy eating habits, maintain appropriate body weight by balancing calorie intake and physical activity, tobacco cessation, reduce alcohol consumption, and ensure adequate sleep. In the control communities, an educational booklet concerning information about diabetes and its risk factors, as well as standard advice about lifestyle change were provided. After the implementation of interventions, a 12-month and 24-month follow-up assessment was conducted [5, 6].

### Data collection instruments and measurements

Most of the measurements undertaken in previous rounds of assessment are also undertaken in this follow-up assessment (Table 1). A detailed description of these measurements has been published [5]. Newly added measurements include an assessment of the retinal microvasculature, ECG, multimorbidity questionnaire, urine albumin, serum creatinine, sedentary behavior, and community engagement/sustainability questions. The measurements used in all rounds of assessment are summarized in Table 1 below.

**Table 1 Tab1:** Measurements included in the four time points of assessment

Variable	Component	Measurement tools/questions	Baseline	12 months	24 months	9-Years
Socio-demography	Age, sex, marital status, education, religion, occupation, household size, and monthly household expenditure		✓	✓	✓	✓
Behavioral measures	Tobacco use	WHO STEPS questionnaire [32]	✓	✓	✓	✓
	Alcohol use	WHO STEPS questionnaire [32]	✓	✓	✓	✓
	Physical activity	Global Physical Activity Questionnaire [33]	✓	✓	✓	✓
	Sedentary behavior	Sitting and screen time	X	X	X	✓
	Sedentary behavior	Time spent in front of a screen [34]	✓	✓	✓	✓
	Diet	Food Frequency Questionnaire [35]	✓	✓	✓	X
Diabetes knowledge	Barriers to healthy eating	Scale designed for trial	✓	✓	✓	✓
	Barriers to PA	Adapted from Booth et al. [36]	✓	✓	✓	✓
	Self-efficacy	Adapted Schwarzer and Renner [37]	✓	✓	✓	✓
Psychosocial measures	Depression	Patient Health Questionnaire-9 [38]	✓	✓	✓	✓
	Stress	Chronic stress scale used in MESA study [39]	✓	✓	✓	✓
	Anxiety	General anxiety disorder scale [40]	✓	✓	✓	✓
	HRQoL	Short Form-36 [41]	✓	✓	✓	✓
	Social support	ENRICHD social support scale [42]	✓	✓	✓	✓
	Life satisfaction	Single question: Satisfaction with life	✓	✓	✓	✓
Medical history	Medical history	CVD and diabetes-related medications	✓	✓	✓	✓
	Family history	Updated family history of disease	✓	✓	✓	✓
	Multimorbidity	Adapted from the WHO SAGE questionnaire [43]	X	X	X	✓
Clinical measures	Anthropometry	Waist circumference (Seca measuring tape)	✓	✓	✓	✓
		Height (Seca stadiometer)	✓	✓	✓	X
		Weight and body composition (TANITA)	✓	✓	✓	✓
		Bioimpedance (TANITA)	✓	✓	✓	✓
	Blood pressure	Omron automatic blood pressure monitor	✓	✓	✓	✓
Biochemical measures	Pathology	Glycaemic control (fasting plasma glucose)	✓	✓	✓	✓
		Glycaemic control -OGTT	✓	✓	✓	X
		Glycaemic control (HbA1c)	✓	✓	✓	✓
		Lipid profile (TBC, HDL, LDL, triglycerides)	✓	✓	✓	✓
		Serum creatinine	X	X	X	✓
		Urine albumin	X	X	X	✓
Assessment of heart conditions		ECG	X	X	X	✓
Retinal microvasculature		Retinal imaging measures(Retinal architecture, arteriolar and venular diameters, and tortuosity) [44]	X	X	X	✓
Mortality		Status and self-reported causes of death	X	X	X	✓
Economic Evaluation	Healthcare utilization	Direct and indirect costs associated with outpatient and inpatient healthcare services, sources of financing, and time away from work due to ill health + SF-36	✓	✓	✓	✓
Community engagement	Sustainability	Sustainability – continued engagement in peer groups/activities; contacts with peer leaders; intention to continue engagement	X	X	X	✓

*WHO* World Health Organization, *SF-36*  Short Form 36, *MESA* Multi-Ethnic Study of Atherosclerosis, *OGTT*  Oral Glucose Tolerance Test, *TBC*  Total Blood Cholesterol, *HDL* High Density Lipoprotein, *LDL* Low Density Lipopotein

### Data collection procedures

#### The research team

The research team consist of three research nurses, a research associate, and a project manager. The team attended a five-day training on the study objectives, data collection tools, and data collection procedures. They have also receive additional training on data entry using RedCap, Retinal Imaging, ECG, and TANITA measurements. Each of these training has practical sessions.

*Phase I (Survey) data collection*: In this phase, the research team collects Questionnaire-based data including weight and BP measurements and biochemical (blood and urine) samples. Members of the research team visit the houses of participants to collect data and samples. The samples are be transferred to A laboratory accredited by the National Accreditation Board for Laboratories(NABL) for testing.

*Phase II (community-based clinics) data collection*: In this phase, we identify fixed facilities in which all the equipment can be placed and organize community-based clinics at these community facilities on specific dates and invite participants to have their measurements (height, body composition analyzer (TANITA), refractometry, retinal measurements, and ECG)undertaken.

### Strategy to reach out to participants after nine years

During the preparation phase of the K-DPP follow-up study, participants were contacted via phone to check their availability and willingness to participate in the follow-up study. Unique K-DPP identification numbers and contact details of the study participants and local resource persons (LRP) from the previous assessments were used to reach to participants. For the survey data collection, the study team visited the homes of participants. Repeat visits are being organized if participants are not available on the first visit. The participants who denied consent are not part of the current evaluation. Concerted efforts to reach out to the missing participants (The participants who are not available at the time of data collection and whose contact details could not be traced) are being made. For community-based clinics, participants are invited to undertake the measurements.

### Long-term effectiveness outcomes

The key study outcomes are the incidence of diabetes and CVD risk at nine years after the intervention. Other primary outcomes include Blood pressure, weight, HbA1c, triglycerides, SF-36, and tobacco. Additionally, body mass index, fat percent, muscle mass, waist circumference, diastolic blood pressure, Fasting Plasma Glucose, lipid profile (total cholesterol, LDL cholesterol, and HDL cholesterol), current alcohol use, diet, and physical activity will be assessed. New measures of pre-clinical retinal microvasculature, heart function and renal disease are also being assessed. We are also considering multimorbidity as a secondary outcome in this follow-up study.

#### Anthropometry and behavioral measures

Anthropometry (weight, total body fat percent, muscle mass, waist circumference) and Blood Pressure are measured using standard protocols. Self-reported physical activity and sedentary behavior are estimated using the Global physical activity questionnaire (GPAQ). Fruit and vegetable consumption, alcohol use, and tobacco use are assessed using the WHO STEPs Questionnaire.

Two TANITA machines (model SC330) used in the previous rounds of assessment were sent to the designated national TANITA service center for recalibration. Weight and body composition parameters will be measured using these TANITA body composition analyzers while the participant is standing still without footwear, with one foot on each side of the scale, facing forward, and arms at their side.

#### Retinal vasculature measurement

A CANON CR-2/Plus/AF RX non-mydriatic retinal camera is being used to obtain retinal images. Two images of each eye are being taken (macular centred and disc centred), following a standard protocol. Image quality will be continuously monitored throughout the study. Images will be graded using fully automated software providing measures of arteriolar and venular diameter and tortuosity. The refractive status of the eyes are being assessed using aCanon RK-F2 Autorefractometer.

#### ECG

We are using ECG equipment (KardioScreen-1612) to acquire the report that is being asssed to determine whether the ECG waves and intervals are normal or pathological. A standard operating procedure adapted from the American College of Cardiology guidelines [45]. KardioScreen records 12-lead ECG and works along with an application on Android Tablet/Mobile. ECGs are being recorded in a standardized way with the patient in the supine position, and leads will be placed. The patient’s clinical history is recorded along with the ECG. The application records ECG readings and stores them on the Cloud. A real-time automatic AI-based software (iMedrix) is fed by the recorded ECGs, and data classification and analytical monitoring of heart health parameters is being done. This includes heart rate [14], PR, QT/QTc, QRS duration, and the specific ECG patterns that occur based on electrophysiological changes in a diseased heart.

#### Biochemistry

All biochemical measurements are following standard procedures. Samples are being centrifuged within 30 min of collection, and transported with dry ice to a nationally accredited laboratory. Plasma glucose are being measured with the Hexokinase method on a COBAS 6000 analyzer, with kits supplied by Roche Diagnostics. The quality of plasma glucose measurements from the proposed laboratory is good for the K-DPP trial; the intra-class correlation coefficient approached 1.0. HbA1c is being measured by High-Performance Liquid Chromatography on a D-10 BIORAD analyzer and lipids by enzymatic methods on COBAS 6000, kits supplied by Roche.

#### Microalbuminuria

The random urine samples are being processed using Roche/Hitachi Cobas 501 analyzer system by Immunoturbidimetric assay with Roche reagent cassettes. Before running the samples, quality control procedures are being followed using Roche precinorm PUC and Precipath PUC. Besides, a monthly Biorad EQAS urine chemistry programme including microalbumin and creatinine is also being followed. Cobas 501 system automatically calculates microalbumin 24-h, random and microalbumin and creatinine ratio.

### Economic evaluation

The economic evaluation involves cost-effectiveness analysis of the intervention from both the health system and societal perspectives. The key outcome measure will be Quality Adjusted Life Years (QALY), which will be estimated using the utility values (SF-6D) derived from the SF-36 survey form. Costs being assessed include both direct medical and non-medical costs and indirect (lost days of productivity) costs associated with the intervention. These are be based on information on staff inputs by duration and type and resource use collected during the study. Any additional “knock-on” effect on hospital admissions or outpatient service use is being quantified and costed for each study participant. We are calculating direct costs to the health service and patients from health facility records, project financial accounts, and participant responses to a survey including questions on health service use and spending. These analyses will be based on updated estimates for health facility costs and personal costs Personal costs to individuals will be collected as part of the questionnaire administered to study participants at nine years. These include transportation costs and out-of-pocket spending for health services use, especially for medications and will capture how the individual financed these costs (e.g., borrowing, asset sales, dis-savings). Any indirect costs to patients arising from being absent from work due to the intervention or illness are also being estimated. Savings from lowered health service use associated with the intervention are subtracted from intervention costs to derive incremental costs at the 9-year mark.

### Program sustainability

We are assessing three key features of K-DPP program sustainability at nine years from intervention using a structured interview with K-DPP participants. This assessment focuses on the past 12 months preceding the assessment. The five main areas of assessment for program sustainability are:Participation in group/educational sessions and/or peer group activitiesContact with peer leaders and/or group membersCurrent and future interest to participate in group sessions/activitiesRecent efforts made in relation to improving lifestyle factorsFactors that would encourage or hinder participation in peer group activities

### Data management plan

#### The survey, biomedical and clinical data

Data are being entered by the research team into the RedCap database at SCTIMST servers. The database has validation checks for the values. Skip patterns are included using branching logic functions. Each team member double-checks the data s/he entered before synchronization. The project manager checks the entered data on weekly basis. Any data entry issues are rectified against the questionnaire. At 25%, 50%, 75%, and 100% of the data entry, the project manager re-checks 10% of the data for quality. After data cleaning is complete, a master copy of the dataset will be created and backed up. All data transformations (derivation of new variables) will be documented in the data dictionary. All hardcopy and electronic data will be properly secured at SCTIMST offices and servers. Data sharing will be based on the guidelines stipulated by the Data Management and Publications committee of the project.

#### Retinal data

Image quality is being continuously monitored throughout the study. Initially, the day’s images were reviewed on site and feedback was provided to the photographer(s) immediately and appropriate measures have been taken to ensure that the images are captured accurately. During subsequent camps / data acquisition during the study, a few images per day are being sent for evaluation and any concerns while taking the photograph will be sent along with the images and a feedback is sent with comments and suggestions within 48 h. In case of any emergency, the contact persons can be contacted for problem resolutions.

Images are being stored on the laptop computer and backed up at the end of each day onto the external hard drive and institutional repository. Each back-up is being labelled by the date of back-up. Apart from quality control images, image transfer is be performed at the end of the study by physical transfer of an external USB hard drive. The best image for each eye will be uploaded into the software for gradeability for each view and then all measurement indices will be obtained.

The data from grading of retinal images will be entered into the RedCap database of the K-DPP Follow-up study. The Participant ID will be used to link the retinal imaging data and the rest of the data from the K-DPP Follow-up study. All data cleaning will be conducted in the same database.

### Statistical analysis

The two co-primary outcomes are diabetes incidence and CVD risk. The analyses will observe the intention-to-treat principle. A generalized estimating equation [46] model with appropriate link function and robust standard errors to account for clustering at polling areas will be fitted to estimate the relative risk (and 95% CI) for the co-primary outcomes at nine years. The sensitivity of the results to assumptions on the missing outcome data underlying this model will be examined using the method of multiple imputations to handle missing data and a pattern-mixture model.

To evaluate the treatment effect on continuous outcomes, a repeated measures mixed-effects linear regression model, adjusting for the baseline measures, will be fitted. Any skewed continuous outcome variable may be transformed before fitting this model. The model will specify treatment, time-point, and treatment by time-point interaction as fixed effects. Random effects will be specified for polling areas, to account for the clustered study design, and for participants, to account for correlation between the repeated measurements on the same participant. The estimated treatment effect (e.g., the absolute difference in means between the treatment arms) at nine years and two-sided 95% CI will be obtained. Binary other outcomes (e.g., diabetes) will be analyzed using GEE models similar to that of the co-primary outcomes.

The retinal image measurements will be compared between the treatment and control groups on the impact of a lifestyle modification program on pre-clinical changes in the retinal microvasculature and its correlation with cardiometabolic risk factors. Retinal imaging measures will include measures retinal architecture such as arteriolar and venular diameters and tortuosity.

The economic evaluation will consist of a cost-effectiveness analysis that will compare the incremental costs and 9-year effects (QALYs) between the study groups. Generalized linear models (GLM) with gamma family and log link components will be used to estimate the incremental costs and QALYs and the results will be presented as incremental cost-effectiveness ratios (ICERs) [47]. QALY models will be adjusted for the baseline utility values (SF-6D). Uncertainty in the cost and QALY estimates will be estimated by non-parametric bootstrapping method [48] and the results will be graphically presented as cost-effectiveness planes and cost-effectiveness acceptability curves. Several sensitivity analyses will be carried out based on different assumptions about the costs, using different discount rates (3%, 5% and 10% per annum), and multiple imputation to assess the sensitivity of the main results due missing cost and QALY data.

Quantitative descriptive analyses will use key indicators—participation in group activities, maintenance of contact with peer leaders, interest to participate in group activities and recent effors made to improve lifestyle factors—to examine the extent of program sustainability from program participants perspectives. Statistical analyses will characterize the relationships among these indicators and the patterns of maintenance of other outcome measures over time.

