## Summary of Kerala Diabetes Prevention Program (K-DPP) findings at 12 and 24 months

The Kerala Diabetes Prevention Program (K-DPP) is a cluster randomized trial of a group-based and peer-led lifestyle intervention among adults at high-risk for type 2 diabetes in Kerala, India [5]. The intervention was adapted from evidence-based lifestyle interventions implemented in high-income countries, namely, Finland, the United States, and Australia [6]. A total of 60 polling areas (1007 participants) were randomized to the intervention arm (500 participants) or control arm (507 participants) in rural Kerala, India. The intervention was administered over 12 months period. Data on sociodemographic factors, lifestyle or behavioral factors, psychosocial, anthropometric, and biochemical measures were collected at baseline, 12 months, and 24 months. Among K-DPP participants, diabetes had developed in 17.1% of control participants and 14.9% of intervention participants (RR = 0.88; 95% CI: 0.66 -1.16, *P* = 0.36) at 24 months [7]. There was a significant reduction in diabetes incidence among a sub-group of participants with impaired glucose tolerance (IGT) (RR = 0.61, 95% CI: 0.41–0.92) in keeping with findings from the landmark clinical trials conducted on people with IGT [8–10]. The K-DPP program was also associated with a 32% reduction in 10-year cardiovascular disease (CVD) risk in the intervention group compared to the control group (RR = 0.68; 95% CI: 0.47–0.99; *P* = 0.047) among those aged 40 years or more [11]. Effectiveness evaluation has demonstrated significant improvements in certain key CVD risk factors and the physical functioning score of the health-related Quality of life (HRQoL) scale [7]. Moreover, this community-based peer-support lifestyle intervention was found to be cost-effective in individuals at high risk of developing diabetes in India over a 2-year period [11, 12]. The implementation evaluation has shown that the K-DPP program was feasible and acceptable in changing lifestyle behaviors in high-risk individuals [13]. Measures of program reach, adoption, and implementation were excellent for K-DPP. Twenty-nine of the 30 intervention communities delivered all intervention components. Two-thirds of intervention participants attended more than 50% of all peer-led group sessions and program recognition was high among local leaders and champions. There was also very strong community engagement and program sustainability in intervention communities at 24 months with 29/30 groups having conducted other diabetes prevention and health promotion activities in their communities [13].

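### The mixed model for continuous outcomes lists no baseline-by-time-point term; if correlation with baseline fades by nine years, the nine-year effect loses a little precision (minor)

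*Protocol article*

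**What the plan says.** In the protocol article, section Statistical analysis, continuous outcomes are to be analysed by "a repeated measures mixed-effects linear regression model, adjusting for the baseline measures, will be fitted". The next statement on the mean model is "The model will specify treatment, time-point, and treatment by time-point interaction as fixed effects". The covariance is described by two terms. One is per area: "Random effects will be specified for polling areas, to account for the clustered study design". The other is per person, given as "for participants, to account for correlation between the repeated measurements on the same participant". The treatment effect is then taken "at nine years and two-sided 95% CI will be obtained".

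Table 1 ("Measurements included in the four time points of assessment") shows baseline, 12 months, 24 months and nine years. With baseline used as a covariate, three rounds remain as responses. The model covers blood pressure, weight, HbA1c, triglycerides and SF-36, which the section Long-term effectiveness outcomes counts among further primary outcomes. Diabetes incidence and CVD risk, the two co-primary outcomes, are analysed by GEE. Retinal measures, serum creatinine and urine albumin are new at nine years and have no baseline value.

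**The concern.** The section describes the model down to a treatment-by-time-point interaction and two levels of random effect, and it includes no interaction of baseline with time-point. A baseline covariate added to that list has one coefficient for all three rounds.

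The rounds are unevenly spaced. Two are early and nearly complete: the sample size section reports loss below 5% at 24 months. The third is at nine years, with 18% and 22% assumed missing. A shared slope is therefore determined mainly by the early rounds, while the effect to be reported is the late one. If a participant's baseline value predicts the nine-year value less well than the 12-month value, the shared slope is too steep at nine years. Two consequences follow: a chance difference in baseline means between arms is over-corrected in the one trial that is run, and the nine-year effect has a somewhat larger variance than it needs to have.

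**Working it through.** **Step 1. The plan's own precision figure.** The sample size section works "With the sample sizes of 415 and 390 participants in the control and intervention arms respectively", with ICC 0.02, 80% power, two-sided 5% and a detectable difference of 0.23 SD.

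- Mean cluster size: 805/60 = 13.4. Design effect: 1 + 12.42 × 0.02 = 1.248.
- SE in SD units: √[1.248 × (1/415 + 1/390)] = 0.0788.
- Detectable difference: (1.960 + 0.842) × 0.0788 = 0.221 with normal quantiles; 0.225 with t on 58 df; 0.227 with t on 58 df, 390 per arm and 13 per cluster.

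The stated 0.23 is reproduced on rounding. It takes no stated credit for baseline adjustment.

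**Step 2. Formula for the nine-year variance.** Set every SD to 1 and let r12, r24 and r9 be the correlations of baseline with each later round. The documents do not give them, so all values below are assumptions. With complete data and a random intercept per participant, the shared slope is b = (r12 + r24 + r9)/3. The nine-year estimate is the nine-year difference in means minus b times the baseline difference. Its variance factors are:

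- shared slope: 1 − 2·b·r9 + b² = 1 − r9² + (b − r9)²
- own slope at each round: 1 − r9²
- no adjustment: 1

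The over-correction per unit of baseline difference is b − r9. Example with 0.70/0.65/0.40: b = 1.75/3 = 0.583, so b − r9 = 0.183. The shared-slope factor is 0.84 + 0.034 = 0.874, against 0.84 for the own slope. The ratio is 1.040 in variance and 1.020 in SE.

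| r12 / r24 / r9 (assumed) | b | b − r9 | variance ratio, shared/own | SE ratio |
|---|---|---|---|---|
| .60/.60/.60 | 0.600 | 0 | 1.000 | 1.000 |
| .60/.60/.40 | 0.533 | 0.133 | 1.021 | 1.011 |
| .70/.65/.40 | 0.583 | 0.183 | 1.040 | 1.020 |
| .80/.75/.50 | 0.683 | 0.183 | 1.045 | 1.022 |
| .70/.65/.30 | 0.550 | 0.250 | 1.069 | 1.034 |
| .80/.75/.40 | 0.650 | 0.250 | 1.074 | 1.037 |
| .80/.80/.20 (extreme) | 0.600 | 0.400 | 1.167 | 1.080 |

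**Step 3. Size on the trial's scale.** With 500 and 507 participants in 60 areas, the baseline design effect is 1 + (1007/60 − 1) × 0.02 = 1.316. The SD of the chance baseline difference is √[1.316 × (1/500 + 1/507)] = 0.072. At .70/.65/.40 a typical over-correction is 0.183 × 0.072 = 0.013 SD, against an SE of 0.0788 × √0.874 = 0.074.

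For power at 0.23 SD (normal formula):

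- .70/.65/.40: 0.878 shared and 0.890 own.
- .80/.80/.20: 0.788 shared and 0.846 own.
- Unadjusted: 0.831.

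**Step 4. Simulation with missing nine-year data.** Several independent simulations used 60 areas, ICC 0.02, about 20% missing at nine years and a random-intercept fit. Variance ratios, shared over own slope, were:

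| r12 / r24 / r9 (assumed) | simulated variance ratio |
|---|---|
| .60/.60/.60 | 1.00 |
| .70/.65/.50 | 1.01 |
| .90/.88/.75 | 1.02 to 1.03 |
| .70/.65/.40 | 0.98 to 1.07 |
| .80/.75/.50 | 1.05 to 1.08 |
| .70/.65/.30 | 1.07 to 1.09 |
| .60/.55/.20 | 1.08 to 1.095 |
| .80/.80/.20 (extreme) | 1.03 to 1.16 |

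At .80/.75/.50 the fitted shared slope was 0.70, steeper than the complete-data 0.683 because the early rounds carry more data. With the interaction, the dependence of the estimate on baseline imbalance fell to within about 0.03 of zero. Mean treatment effects were within 0.004 of zero under both models. The spread between simulations shows that the gain also depends on further assumptions, such as the correlations among the later rounds.

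**The case against.** The strongest objection concerns the reading. The article never says that the slope is shared. Adjustment for baseline leaves the form of the covariate open, an interaction with time-point would contradict nothing in the text, and an article may leave such coding to an analysis plan that is not shown. This stands in part: the shared slope is inferred from the list of effects, not stated. The inference is still a fair one, because the section chose to spell out the interactions in the mean model and named only one.

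The second objection concerns size. Fading correlation is an assumption, the loss disappears when correlations are equal, and percentages of variance look larger than percentages of SE. One pair of simulation runs at .70/.65/.40 found no loss at all (SE 0.0651 shared, 0.0657 own). The two estimates differed with an SD of only 0.008 to 0.022, against an SE of 0.05 to 0.08, so a conclusion would seldom turn on the choice. All of this stands, and it is why the point is minor.

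The third objection is that planned power does not rest on baseline adjustment, and that a shared slope is still better than no adjustment in every case of the closed-form table except the extreme one. That also stands. A reader might infer that the 0.23 SD figure is undermined; the documents do not support this.

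**Conclusion.** The point holds as a minor one about efficiency. As written, the mean model has one baseline slope for three unevenly spaced rounds. If correlation with baseline fades by nine years, that slope over-corrects a chance imbalance and costs roughly 0 to 9% of the variance of the nine-year effect, or 0 to 4% of its SE. The highest ratio outside the extreme case was 1.095, which is √1.095 = 1.046 in SE. Only a very steep fall in correlation, such as 0.80 to 0.20, could cost more. These sizes rest on assumed correlations and on a random-intercept fit.

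A reader might infer that the nine-year treatment effect is biased. It is not: under randomisation the baseline difference averages zero, so any slope leaves the estimate centred on the true effect. The over-correction is a feature of one realised trial. Nor does the point reach the trial's main result, because the co-primary outcomes use GEE. It also cannot apply to measures first taken at nine years.

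**What to change.** In the Statistical analysis section, add a baseline-by-time-point interaction to the fixed effects for continuous outcomes that were measured at baseline, and state that the nine-year treatment effect is estimated from that model.

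The cost is two extra degrees of freedom with about 805 participants expected at nine years, and no new data. With equal correlations the simulated variance ratio was 1.00. In the least favourable simulation the interaction raised the SE by about 1% (0.0657/0.0651 = 1.009). The sponsor already holds the baseline, 12- and 24-month data and can look at the fall in correlation between those rounds now. Settling the term before the nine-year data are analysed also closes an open modelling choice.

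The change does not repair a misspecified residual covariance. In simulations with only a random intercept per participant, nominal 95% intervals covered 0.91 to 0.92 at .70/.65/.40 and 0.84 to 0.87 at .80/.80/.20, with or without the interaction. That needs its own attention.
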